### Trial design

Randomised control participant-blinded, single-centre, feasibility trial with two parallel groups (FMT capsules and matched placebo). Eighty patients will be randomised 1:1 (40 will receive FMT capsules and 40 placebo) from eligible patients identified from Guy’s and St Thomas’ hospitals (figure 1 and box 1).

Box 1Participant inclusion/exclusion criteria**Inclusion criteria**To be eligible for enrolment, a participant must meet all the following criteria before undergoing any study-related procedures:Adult patients (age 18 years or older at time of consent).Current/previous patient at Guy’s and St Thomas’ NHS Foundation Trust.Ability to understand the purpose, potential benefits and risks of the study and capable of giving informed consent. The participant must be able to provide written informed consent.Documented gastrointestinal carriage of ESBL-E or CPE (stool sample) in the 21 days prior to consent.Symptomatic infection with the same target organism of interest in preceding 6 months (this needs to be microbiologically confirmed but is not restricted to any particular body site for example, could be urinary tract infection, intra-abdominal infection, blood stream infection).**Exclusion criteria**Pregnancy or planned pregnancy.Breastfeeding.Severe or life-threatening food allergy.Allergy or other contraindication to omeprazole, investigational medicinal product (IMP) or placebo ingredients.Treatment with systemic antibiotic on the day of and day prior to first IMP/placebo dosing to the end of the dosing period.Treatment with pre or probiotics in the 4 weeks prior to randomisation and for the duration of the study.Severe immunodeficiency.Systemic chemotherapy <30 days from baseline or planned chemotherapy within the upcoming 6 months.Known HIV infection with CD4 count <250 cells/uL.Known neutropenia with absolute neutrophils <1.0×10^9^.Prolonged treatment with corticosteroids (equivalent to prednisone >60 mg daily for >30 days) within 8 weeks of randomisation.Life expectancy <6 months.Swallowing disorder, oral-motor dyscoordination or likely inability/unwillingness to ingest study medication.Patients who have received another investigational drug or device within 4 months prior to randomisation.Any condition or circumstance, in the opinion of the investigator, that would compromise the safety of the patient or the quality of the study data.

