## Methods and analysis

### Primary objectives

The primary objective of this study is to determine the feasibility and acceptability of administering encapsulated FMT to participants colonised with ESBL-E/CPE. This will be used to determine if a substantive trial is feasible.

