### Primary endpoints

The primary outcome measure is consent rate (as a proportion of patients who fulfil inclusion/exclusion criteria). The success criteria for the primary endpoint are stratified. If <15% is achieved, progression to a substantive trial will not be deemed feasible. If 15%–39%, progression to a substantive trial will be deemed feasible with protocol modifications and clearly defined stop/go criteria. An overall consent rate of >40% will be taken as indicating a substantive trial is feasible.

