### Patient and public involvement

Patients and the public have identified AMR as a research priority and were involved in identifying the research question and providing feedback on the grant application. A patient representative has been appointed to the Trial Steering Committee (TSC), and has advised on the design of the research, the protocol and all patient facing materials. The patient representative will also be involved in dissemination of the study findings. As the acceptability of FMT in this setting is a key research question, we will invite up to eight patients to participate in focus groups. The aim of the group will be to understand their experience in participation in the study and will focus on acceptability, barriers to participation and improvements that could be made to any resulting substantive trial.

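### A patient unwilling to take the capsules can be logged as ineligible instead of as a non-consenter, so the primary consent rate may overstate acceptability

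*Protocol article*

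**What the plan says.** The Primary objectives section sets out to "determine the feasibility and acceptability of administering encapsulated FMT to participants colonised with ESBL-E/CPE". The Patient and public involvement section repeats the emphasis: "As the acceptability of FMT in this setting is a key research question".

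Under Primary endpoints the measure is fixed: "The primary outcome measure is consent rate (as a proportion of patients who fulfil inclusion/exclusion criteria". Three bands follow:
- Stop: "If <15% is achieved, progression to a substantive trial will not be deemed feasible".
- Amend: "If 15%–39%, progression to a substantive trial will be deemed feasible with protocol modifications".
- Go: "An overall consent rate of >40% will be taken as indicating a substantive trial is feasible".

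Box 1, under Trial design, includes this exclusion: "Swallowing disorder, oral-motor dyscoordination or likely inability/unwillingness to ingest study medication". It puts physical inability and expected unwillingness in one item.

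Three other sections bear on who is counted. Consent places informed consent ahead of eligibility screening. Sample size assumes a 40% rate among about 200 eligible patients approached. Data synthesis, analysis and presentation describes the reported proportion as those who accept when randomisation is offered, with an exact binomial interval. No section says how a patient excluded for unwillingness is treated in the primary rate.

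**The concern.** In an efficacy trial an exclusion for expected non-adherence is routine. Here the quantity being measured is willingness, and the eligibility rule that defines the denominator is partly a judgement about that same willingness. Read together, the endpoint definition and Box 1 allow one refusal to be recorded in two ways: as a decline, which lowers the consent rate, or as an exclusion, which leaves no trace in it. The article gives no rule separating the two.

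The refusals that can disappear are those that speak most directly to whether encapsulated FMT is acceptable. The rate drives the progression decision, and the expected value of 40% sits at the go threshold, so a small shift can change the band.

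**Working it through.** **Inputs.** From the protocol: expected rate 40% with 95% CI 33 to 47 and about 200 eligible patients approached (Sample size); exact binomial method (Data synthesis, analysis and presentation); bands <15%, 15%–39% and >40% (Primary endpoints). Assumed, because the protocol gives no figure: *k*, the number of otherwise eligible patients excluded only for unwillingness.

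**1. The plan's own interval.** 40% of 200 is 80 consents.
- Normal approximation: 0.40 ± 1.96 × √(0.40 × 0.60/200) = 0.40 ± 0.068, or 33.2% to 46.8%.
- Exact binomial: 33.2% to 47.1%.

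Both agree with the stated 33 to 47.

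**2. Direction.** Let *C* be consents and *N* the otherwise eligible patients, including the unwilling. If everyone counts, the rate is *C/N*. If *k* refusers are excluded before consent, it is *C/(N − k)*, which is larger for any *k* > 0.

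**3. How many exclusions change the band, with *N* = 200.** To exceed 40%, *k* must exceed 200 − *C*/0.40. To reach 15%, *k* must be at least 200 − *C*/0.15.

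| Rate with all counted | Refusers | Smallest *k* | Reported rate | Band change |
|---|---|---|---|---|
| 78/200 = 39% | 122 | 6 | 78/194 = 40.2% | amend to go |
| 76/200 = 38% | 124 | 11 | 76/189 = 40.2% | amend to go |
| 70/200 = 35% | 130 | 26 | 70/174 = 40.2% | amend to go |
| 60/200 = 30% | 140 | 51 | 60/149 = 40.3% | amend to go |
| 28/200 = 14% | 172 | 14 | 28/186 = 15.1% | stop to amend |

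Close to a threshold a few reclassified refusals suffice (6/122 = 4.9% of refusers at 39%). Further away it takes many (51/140 = 36.4% at 30%).

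**4. Restoring *k* unwilling patients to the planned 80/200.**

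| *k* (assumed) | Rate | Exact 95% CI |
|---|---|---|
| 0 | 80/200 = 40.0% | 33.2 to 47.1 |
| 10 | 80/210 = 38.1% | 31.5 to 45.0 |
| 20 | 80/220 = 36.4% | 30.0 to 43.1 |
| 40 | 80/240 = 33.3% | 27.4 to 39.7 |

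This table shows the size of the shift only. Its starting value of exactly 40.0% is not above 40%, so it does not show a move from go to amend; step 3 shows changes of band.

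**5. The case that runs the other way.** If *m* patients consent and are then excluded on this ground, they leave numerator and denominator together: *(C − m)/(N − m)*. With *m* = 5, 80/200 becomes 75/195 = 38.5%, a fall. The upward shift therefore depends on the exclusion being applied before consent.

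**The case against.** The strongest reply is that a patient who hears the offer and says no has simply declined. Consent comes before screening, so Box 1 would not yet have been formally applied. The Sample size section thinks in terms of patients approached, and the analysis section in terms of accepting an offer. On that reading refusers stay in the denominator. The criterion also says likely unwillingness and opens with swallowing disorders, so it can be taken as a judgement about managing the capsules and not as a label for people who decline FMT. Heavy use of the exclusion would also lower the proportion meeting the criteria, which is a secondary feasibility endpoint.

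Much of this stands, and it makes the bias conditional. It does not settle the definition. The Sample size section still says eligible, and the primary endpoint still requires the criteria to be met. If decliners are never screened, it is unclear how they enter a denominator of patients who meet those criteria. The secondary eligibility proportion does not enter the consent-rate bands, and the article does not split it by reason.

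A reader might infer that the consent rate is necessarily biased upward, or that a reported 40% conceals a true rate of 33%. The protocol supports neither. No passage tells staff to recode refusals as exclusions, step 5 shows a sequence with the opposite effect, and the counts behind 33% are assumed.

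**Conclusion.** The point holds in conditional form. The stated definition of the primary endpoint, combined with Box 1, lets an unwilling patient be classed as ineligible, and nothing in the article returns that patient as a non-consenter. To the extent that this ground is used before consent, the consent rate overstates acceptability.

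The size is unknown and could be negligible if staff rarely use the ground. Within the assumed range of 10 to 40 such patients beside 80/200, the rate with them counted would be 38.1% to 33.3%. The practical risk is greatest near a threshold, where 6 of 122 refusers at a 39% rate, or 14 of 172 at 14%, are enough to change the band. A move from amend to go changes the conditions for a substantive trial; both bands allow one to proceed. Exclusion for physical inability to swallow is not in question.

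**What to change.** Leave the eligibility criterion as it is and define the primary denominator explicitly. Patients who are otherwise eligible, and whose only reason for exclusion is unwillingness to take FMT or placebo, count as eligible and not consenting. Record unwilling and unable as separate reasons on the screening log, and report the number in the first group beside the consent rate.

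The cost is one sentence in the endpoint definition and one reason code on the log. The code should be in use from the start of screening, because the two reasons cannot be reliably separated afterwards if they were not recorded. The downside is that the reported consent rate may be lower.

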**Figure 1 F1:**
[figure not shown]
Consolidated Standards of Reporting Trials flow diagram. FMT, faecal microbiota transplant.

### Patient and public involvement

Patients and the public have identified AMR as a research priority and were involved in identifying the research question and providing feedback on the grant application. A patient representative has been appointed to the Trial Steering Committee (TSC), and has advised on the design of the research, the protocol and all patient facing materials. The patient representative will also be involved in dissemination of the study findings. As the acceptability of FMT in this setting is a key research question, we will invite up to eight patients to participate in focus groups. The aim of the group will be to understand their experience in participation in the study and will focus on acceptability, barriers to participation and improvements that could be made to any resulting substantive trial.

### Patient population

Participants will be recruited from Guy’s and St Thomas’ NHS Foundation Trust, a 1200 bed academic centre in central London. It is anticipated that most patients will already be admitted to the hospital as part of standard of care treatment, thus, most activities will take place on the ward or clinical area that the patient is already located. Where this is not the case, participants will be invited to attend the infection clinical room on an outpatient basis.

### Consent

Informed consent (for both healthy donors and patient-recipients) will be obtained prior to any trial related activities, including screening for eligibility. Potential participants will be given the participant information sheet and allowed enough time to read thoroughly and discuss with others outside the study team (eg, family, friends and general practitioner) (see online supplementary table 2). Participants are free to withdraw from the trial at any time without giving reasons. Data and samples collected up to the point of withdrawal will only be used after withdrawal if the participant consented for this. Patients who lack capacity will not be enrolled in this study. Where a participant consents but later becomes incapacitated, the original consent given endures the loss of capacity, providing that the trial has not significantly altered.

### Randomisation

The randomisation schedule will be generated using a validated online randomisation programme, hosted by King’s Clinical Trials Unit. The method of randomisation will be block randomisation with randomly varying block sizes. As this is a single-centre study, randomisation does not need to be stratified. Participants will be allocated treatment as close as possible to receiving it.

### Study intervention

FMT for this trial will be prepared in a lyophilised, encapsulated form in accordance with Good Manufacturing Practice principles and under manufacturing authorisation for an IMP from the Medicines and Healthcare Products Regulatory Agency. Our centre has recently provided FMT for a Clinical Trial of an Investigaional Medicinal Product (CTIMP) for cirrhosis and this follows similar processes.^20^ Healthy donor inclusion and exclusion criteria and screening and eligibility questionnaire are described in online supplementary table 3 and 4.

The product contains 0.9% sodium chloride and 5% trehalose (cryoprotectant) as excipients. A minimum of 80 g faeces from each donor will be used to manufacture one batch of five capsules. Following lyophilisation, the material will be encapsulated in five size 0 delayed release methylcellulose capsules (DRcaps, Capsugel, Livingston, UK). Placebo capsules will contain microcrystalline cellulose. The capsules for the FMT and placebo will be identical in appearance. The capsules are coloured Swedish orange, resulting in an opaque appearance through which the contents cannot be seen.

FMT donors are carefully screened healthy volunteers with a body mass index between 18 and 30. Donors undergo questionnaire screening for risk factors and testing for a range of infectious agents as previously described and in accordance with national guidelines (see appendix A for full details).^21^ FMT material is traceable from donor to recipient. Aliquots of donor stool will be kept for 30 years to allow for future testing if required.

At baseline, participants will have their medication history recorded, including over the counter preparations and supplements as well as pre/probiotics. Vital signs, height and weight and baseline blood biochemistry and haematology will be collected. Additionally, a serum sample will be stored to allow future testing in the event of a possible transmission event. If female and of childbearing age, a urinary pregnancy test will be performed. An EQ-5D questionnaire will also be administered.

Encapsulated FMT (IMP) and placebo will be dispensed by study staff to trial participants over 3 consecutive days (or over 5 days if over a weekend). Patients will be fasted for 4 hours and be pretreated with omeprazole on the morning on the FMT (40 mg on first dosing day and 20 mg on the 2 subsequent dosing days).

It is anticipated that most patients will remain an inpatient for the duration of treatment. If they have been discharged in the interim, provision will be made for them to attend for treatment as an outpatient.

### Evaluations during and after treatment

Follow-up events will be scheduled for all participants at 1 week, 1 month, 3 months and 6 months after end of therapy. If an outpatient, the visits at 1 week, 3 months and 6 months will be conducted by telephone, with the participant returning a stool sample by post. The follow-up at 1 month will be face to face and will include a blood sample for immune analyses. All visits will involve completion of an EQ-5D questionnaire (see figure 2 for additional details).

**Figure 2 F2:**
[figure not shown]
Intervention and follow-up. FMT, faecal microbiota transplant.

### Sample analyses

Stool samples will be analysed for the presence of ESBL-E/CPE using culture based (chromogenic agar with species identification using MALDI-ToF mass spectrometry and phenotypic antimicrobial susceptibility testing) and molecular techniques (multiplex PCR panel for 16 ESBL/CPE resistance genes).

### Follow-up

If a participant fails to present for follow-up assessment, all attempts to contact the participant and information received during contact attempts will be documented in the participant’s medical record. In any circumstance, every effort will be made to contact the participant and document outcome (ie, three documented contact attempts via phone calls, on separate occasions will be made to locate or contact the participant, and/or determine health status). Stool samples will be stored for further follow-on analysis, including metagenomics and metabolomics profiling.

### Qualitative study

A qualitative study of participant’s experiences will be undertaken and comprises a focus group interview with a minimum of eight participants. Ideally, the group will include at least two patients who were approached but did not agree to participate. The aim of these discussions is to identify facilitators and barriers to delivering the trial, and whether there are any aspects of the trial that should be changed. The interviews will be semistructured and recorded to aid writing up the study report. Objectives of the focus group will include identifying ways of increasing recruitment and retention; identifying ways of broadening participation in the trial to improve diversity of population; improving understanding of how participants join trials and experience of participation; measuring reasons for non-adherence to the trial medication; exploring stakeholders’ views of acceptability of the trial design; strengthening the ethical conduct of the trial, for example, informed consent procedures; addressing any local issues which may impact on the feasibility of a substantive trial.

## Statistical analysis

### Sample size

As this is a feasibility study, significance tests between or within groups will not be performed for the study’s primary and secondary endpoints, therefore a power calculation has not been performed. For feasibility and pilot studies, sample sizes between 24 and 50 have been recommended to estimate a chosen parameter.^22 23^ We have chosen a 1:1 treatment to placebo ratio, therefore a total sample size of 80 would be enough to estimate the SD of the outcome in 40 treated patients, allowing for some loss to follow-up. We will also be able to estimate our expected recruitment rate of 40% (95% CI: 33 to 47) if we approach around 200 eligible patients.

### Data synthesis, analysis and presentation

A statistical analysis plan will be written by the trial statistician and signed off prior to database lock. The study will be reported in accordance with the Consolidated Standards of Reporting Trials extension for pilot and feasibility studies.

The proportion of patients who accept the offer of randomisation will be reported with 95% CIs computed by the exact binomial method. No statistical tests for significant differences between treatment groups will be performed. In addition to summary statistics of the secondary outcomes, all harms and withdrawals will be reported with 95% CIs. Patients will be analysed in the groups to which they are randomised in accordance with intent to treat principals.

The protocol has been designed to place minimal burden on patients and case report forms are only capturing essential data. It is inevitable that there may be some missing data, which will be reported by treatment group with reasons for missingness described, where possible. Since this is a feasibility study, we do not plan to impute missing data.

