**Trial registration number:**

ISRCTN registration number 34 467 677 and EudraCT number 2019-001618-41.

Strengths and limitations of this studyThe randomised, placebo-controlled design will control for spontaneous loss of carriage of resistant organisms.Qualitative data from participant focus groups will inform and influence a potential future trial.This study will assess feasibility; however, it is not statistically powered to assess clinically efficacy, which will need to be evaluated in a substantive trial.Mechanistic outcomes using metagenomic, metabolomic and host immune analyses could provide insight into the mechanism of action of Faecal microbiota transplant in treatment responders.The lack of investigator blinding, and the single-centre design is a limitation.

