### Trial monitoring groups

#### Trial management group

Comprises the chief investigator (CI), trial statistician, trial staff and other lead clinical and non-clinical coinvestigators and coapplicants. The TMG are responsible for the day-to-day management of the trial and to ensure that all practical details of the trial are progressing and working well. The TMG will monitor all aspects of the conduct and progress of the trial, ensuring that the protocol is adhered to and take appropriate action to safeguard participants and the quality of the trial itself. The TMG will be responsible for drafting of the final report and submission for publication.

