#### Trial Steering Committee

A TSC will be convened with membership nominated by the CI in partnership with the sponsor. The role of the TSC is to provide overall supervision for the trial on behalf of the sponsor and funder and to ensure that the project is conducted to the rigorous standards set out in the Department of Health and Social Care’s Research Governance Framework for Health and Social Care and the Guidelines for Good Clinical Practice. The committee Chair will be independent of the study. The committee will also comprise four other independent members (Consultant Microbiologists or Gastroenterologists), a patient/public representative and an independent statistician.

The TSC will take responsibility for monitoring data and making recommendations to the TMG on whether there are any ethical or safety reasons why the trial should not continue. A separate Data Monitoring and Ethics Committee will not be established as this is a single-centre feasibility trial with a relatively small number of patients using an established IMP with a relatively well described safety profile.

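### Sign-off of the analysis plan is tied only to database lock, which comes after the consent count is known, while the definition and bands of the consent rate are still loose at the expected 40%

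*Protocol article*

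**What the plan says.** The section on data synthesis, analysis and presentation sets the deadline: "A statistical analysis plan will be written by the trial statistician and signed off prior to database lock".

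On blinding, the trial design section describes a "Randomised control participant-blinded, single-centre, feasibility trial with two parallel groups (FMT capsules and matched placebo", and the strengths and limitations box concedes: "The lack of investigator blinding, and the single-centre design is a limitation".

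On roles, the trial management group "Comprises the chief investigator (CI), trial statistician, trial staff and other lead clinical and non-clinical coinvestigators and coapplicants", and "The TMG will monitor all aspects of the conduct and progress of the trial". Outcome monitoring is placed elsewhere: "The TSC will take responsibility for monitoring data and making recommendations to the TMG". The steering committee (TSC) includes an independent statistician.

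On the primary outcome there are two descriptions. Under primary endpoints: "The primary outcome measure is consent rate (as a proportion of patients who fulfil inclusion/exclusion criteria". In the analysis section: "The proportion of patients who accept the offer of randomisation will be reported with 95% CIs computed by the exact binomial method". The consent section places consent before screening for eligibility. The progression bands are below 15%, 15%–39%, and above 40%. The sample size section expects 40% (95% CI 33 to 47) from about 200 eligible patients approached.

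**The concern.** A deadline of database lock protects an analysis when lock is also the moment at which results become known. In this trial it is not. Investigators know allocation throughout, and the primary outcome is a recruitment count that the team running the trial must follow to do its job. Consent precedes dosing, and the last follow-up is 6 months after the end of therapy, so the count is final about six months before the last data arrive. The stated rule allows the plan to remain unsigned for all of that time.

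This would matter little if the primary rate were fully fixed in the protocol. It is not: the numerator can be read in two ways, the denominator depends on patients whose eligibility is formally checked only after they consent, and the bands leave a gap at the value the trial expects. What is at stake is whether the progression verdict rests on a rule fixed beforehand or on a reading chosen with the count known.

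**Working it through.** **Inputs.** 80 to be randomised (trial design); about 200 eligible patients approached and an expected 40%, 95% CI 33 to 47 (sample size); bands <15%, 15%–39%, >40% (primary endpoints); exact binomial interval (analysis section); last follow-up 6 months after end of therapy (evaluations during and after treatment).

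**Step 1: the plan's own figure.** With x = 80 and n = 200, the rate is 80/200 = 40.0%. The exact limits are the 0.025 quantile of Beta(x, n − x + 1) = Beta(80, 121) and the 0.975 quantile of Beta(x + 1, n − x) = Beta(81, 120), which give 33.2% and 47.1%. The stated 33 to 47 reproduces.

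**Step 2: where the expected result falls.** 40.0% is above 39% and not above 40%, so read literally it belongs to no band. With n = 200 the counts in the gap are 79 (39.5%) and 80 (40.0%). For X ~ Binomial(200, 0.40):

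- P(X = 79 or 80) = 0.115, no band;
- P(X ≥ 81) = 0.469, upper band;
- P(X ≤ 78) = 1 − 0.469 − 0.115 = 0.416, middle band or lower.

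**Step 3: how little a change of definition needs to be.** The counts below other than 80/200 are assumed for illustration.

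| Reading | Rate | Band |
|---|---|---|
| 80/200 (randomised of eligible) | 40.0% | none |
| 81/200 (one consenter not randomised) | 40.5% | >40% |
| 84/200 (four consenters not randomised) | 42.0% | >40% |
| 80/190 | 42.1% | >40% |
| 80/199 | 40.2% | >40% |
| 80/201 | 39.8% | none |
| 80/206 | 38.8% | 15%–39% |
| 80/220 | 36.4% | 15%–39% |

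The two numerators need not agree, because a patient can consent and then fail screening or withdraw before randomisation. A secondary endpoint also counts those receiving FMT or placebo as a percentage of those consenting, so the protocol itself allows for loss after consent.

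**Step 4: timing.** Every consent is given before dosing, and the last visit is 6 months after the end of therapy. All quantities in Step 3 are therefore known to those running recruitment about six months before the last visit, and lock cannot sensibly come before that visit. The stated rule permits sign-off after this point.

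These figures show how close the expected result lies to the line. They do not measure an effect of the sign-off date, which cannot be computed from the documents.

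**The case against.** The strongest reply is that sign-off before lock is common wording, contradicts nothing in the article, and leaves little of substance open. The protocol already fixes three progression bands, an exact binomial interval, analysis as randomised, no imputation, no between-arm tests, and the carriage endpoints with their days. Much of this stands, and it is why the point is minor. What it does not cover is the wording of the primary rate and the gap in its bands.

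A second reply is that blinding has nothing to do with a pooled consent rate, which a team would see accrue even in a double-blind trial. This is correct. For the primary outcome the argument rests on timing and loose definition alone, and it means that only an earlier fix protects that outcome.

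A reader might go further and infer that the statistician, as a member of the management group, sees carriage by arm and could build the plan around the most favourable of the eight carriage readouts (culture and PCR at four days). The document does not support that. It does not state the statistician's blinding status or send arm-level outcomes to the management group, and it gives data monitoring to the TSC. All eight readouts are listed as secondary endpoints, and summary statistics of the secondary outcomes are promised. The secondary objectives openly intend the data to help choose the future trial's efficacy outcome, so an earlier sign-off date would not remove that use. Missing-data handling is also largely settled: missing data are to be reported by group, with reasons where possible, and not imputed.

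**Conclusion.** The concern holds as a minor improvement to a stated rule. Lock is a late deadline for a trial with unblinded investigators whose decisive outcome is known about six months before the last visit. It combines with two descriptions of the primary rate and a band gap at the expected 40%. If the true rate is 40% and 200 eligible patients are approached, there is about an 11.5% chance of a result in no band, and near that value a difference of one patient in numerator or denominator can move the reading.

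This assumes that the bands are read literally and that consent and randomisation counts can differ. It makes no claim that anyone intends a late choice, that the statistician is unblinded, or that the carriage results would be biased. The visible progression rule concerns consent only; the full criteria are in a supplementary table that is not shown.

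**What to change.** Replace the sentence on sign-off with: *The SAP will be signed off before the first participant is randomised or, if recruitment has started, before carriage or harms are tabulated by arm; later changes will be dated, justified and reviewed by the independent TSC statistician.*

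The fallback alone would leave the running consent rate exposed, so also amend the protocol now to fix:

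- **Numerator:** written consent or randomisation, one of the two, used in both the endpoint and analysis sections.
- **Denominator:** which patients count as fulfilling the criteria, and how this is judged for those who decline before screening.
- **Band edges:** contiguous limits, stating on which side exactly 40% and values between 39% and 40% fall.

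The cost is that the SAP is written earlier and any later change needs a dated amendment. No extra post is needed, because the TSC already has an independent statistician.
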